### Outcomes

The primary outcome will be the difference in anemia cure rate between the experimental arms at the end of 6 months from the intervention’s start, in children found to be anemic at baseline. In addition, we will assess several secondary outcomes occurring along the hypothesized causal pathway of the intervention effect (Fig. 2), including: 1) difference in changes of knowledge and practice of mothers of anemic children from baseline to follow-up, 2) differences in the estimated 24-hour dietary iron intake among anemic participants exposed and not exposed to the intervention, 3) difference in net improvements in individual hemoglobin values between baseline and 6 month follow-up among anemic children exposed and not exposed to the intervention, 4) net improvements in mean ferritin values among anemic participants exposed and not exposed to the intervention, and, 5) difference in the cluster level anemia prevalence between experimental arms. Additional process indicator data include evaluation of the proportion of expected IFA doses delivered to children in the study (adherence to iron treatment), maintenance of LHW records of delivery of the intervention and IFA, and recording of the incidence of side effects of IFA supplements in children. Qualitative research on the acceptability, perceptions, and experiences of the LHWs regarding the training for and the actual delivery of the intervention will be conducted using focus group discussions. These data will help identify key assumptions and limitations of underlying intervention feasibility and sustainability and scaling-up, particularly when involving LHWs at the national level.

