#### Exclusion criteria

Children with severe anemia defined as Hb ≤ 7.9 gm/dl for the purpose of this trial [40] will be excluded and referred to the primary health center/first referral unit for assessment and medical management. Children with a reported history of an active infection or fever >101 °F will also be excluded from participation and referred to the primary health center/first referral unit for management as usual.

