**Fig. 2 Fig2:**
[figure not shown]
Hypothesized causal pathway of the effect of the intervention and its outcome measures

Furthermore, the intervention benefits are hypothesized to spill over to the entire community. Following a socio-ecological framework [45, 46], the child’s immediate environment affected by the intervention would be the microsystem (the family) and the mesosystem (for example, parent-teacher meetings, the neighborhood, and social gatherings at the village level). At both these levels, one could expect counseled mothers of anemic children to modify the behaviors of mothers of non-anemic children, with respect to IFA consumption and dietary iron intake, thereby reducing the overall prevalence of anemia at the cluster level. Thus, the intervention is evidence based, contextually relevant, uses locally relevant resources, and has the potential to influence national policy.

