### Components of the Intervention

i)*Enrollment and screening for anemia*All eligible participants providing informed consent will be enrolled in the trial, provide information for a baseline questionnaire, have anthropometric measurements, and venous blood obtained by phlebotomy to screen for anemia by the research team.ii)*Iron supplementation*A core preventive measure common to both trial arms is the delivery of iron supplements. All enrolled non-anemic participants are eligible for IFA supplements (tablets containing 20 mg elemental iron, 8 tablets/month) in line with National Iron + guidelines [25]. The guidelines recommend 20 mg IFA dispensed as syrup biweekly throughout the period 6–60 months and deworming for children 12 months and older. Since IFA syrup was not available in Karnataka, for the purpose of this trial, IFA is provided as 20 mg tablets. All enrolled participants detected with anemia (Hb ≥ 8 and ≤ 11 gm/dL) [40] in both arms of the trial are eligible for the therapeutic IFA dosage to control iron deficiency anemia (tablets containing 20 mg elemental iron, 20 tablets/month for 5 months). All subjects with acute infections or fever will be excluded during enrollment to the trial. Furthermore, during dispensation of IFA tablets, LHWs will advise mothers to withhold these during periods of fever or acute infections.iii)*Education and counseling*Only mothers/caregivers of anemic children (Hb ≥ 8 and ≤ 11 gm/dL) in the intervention arm will receive five monthly education and counseling sessions delivered by the LHW over the 6-month intervention period (Fig. 1).iv)*Monitoring of adherence to IFA*From the second counseling visit onward, LHWs in the intervention arm perform monthly pill counts to assess adherence to IFA dispensed only to mothers/caregivers of anemic children in the previous month and document the side effects of IFA, if any. In accordance with precautions in the guidelines, LHWs will advise mothers to withhold supplemental and treatment IFA during periods of fever or acute infections. A similar monthly assessment of adherence for mothers of anemic children in the control arm will not be performed. However, at the end of the 6 months of intervention, an assessment adherence to IFA in the previous 30 days will be performed for all participants in both arms of the trial.

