### Statistical methods

#### Statistical power and sample size calculation

Primary analyses are limited to children with anemia at enrollment. At the end of 6 months, a difference of at least 12 % in the cure rate of anemic children is required if the intervention is considered to have sufficient public health utility to warrant its cost and effort [47–49]. We estimate that the 12 % reduction in proportion of anemic children at 6 months would occur due to a cure rate of 30 % in the control group (IFA alone) and 42 % in the experimental arm where children receive IFA plus the community-based parental intervention. To detect a 12 % difference in 6-month anemia cure rates at an alpha level of 0.05 for a two-tailed test, with 80 % power, a total unadjusted sample size of 500 children with anemia is required, which after adjustment for clustering (design effect = 2.2) results in a sample size of 1,100 children with anemia. The design effect assumes an intracluster correlation coefficient (ICC) of 0.05 and 25 participating children with anemia per village. The anticipated degree of intracluster correlation was selected based on results from several recent trials of interventions on anemia [47–49]. We further allow for a 10 % loss to follow-up of children identified with anemia at baseline, yielding a final sample size of 610 children with anemia per arm (1,220 in all). We will recruit 30 clusters per trial arm to accommodate potential losses of clusters if LHWs should stop working, resulting in loss of an entire cluster. Thus, power will be greater than 80 %. Analyses will also consider prevalence of anemia at 6 months among all participating children regardless of their baseline anemia status. Based on an estimated prevalence of 50 % anemia at baseline in each village, the number of children required will be 1,220 in each trial arm.

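### Pooled cluster prevalence is a total effect: it differs by 6 points with no spillover, and no listed outcome isolates children not anemic at baseline

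*Protocol article*

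**What the plan says.** The rationale for the intervention (text after Fig. 2) sets out a spillover hypothesis: "the intervention benefits are hypothesized to spill over to the entire community". It names the route, in that "one could expect counseled mothers of anemic children to modify the behaviors of mothers of non-anemic children", and the expected result, "thereby reducing the overall prevalence of anemia at the cluster level".

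Counseling itself goes to one group. Under Components of the Intervention, only mothers or caregivers of anemic children "in the intervention arm will receive five monthly education and counseling sessions delivered by the LHW".

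Under Outcomes, the fifth secondary outcome is the "difference in the cluster level anemia prevalence between experimental arms". The section introduces the secondary outcomes as lying along the causal pathway of the intervention. Outcomes 1 to 4 are restricted there to anemic children or their mothers. The abstract instead describes the secondary outcomes as comparisons of all participants. Neither version defines an outcome for children who were not anemic at baseline.

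The sample size section gives the population for prevalence: "Analyses will also consider prevalence of anemia at 6 months among all participating children regardless of their baseline anemia status". Children with severe anemia "will be excluded and referred to the primary health center/first referral unit for assessment and medical management", and follow-up hemoglobin is taken from participants only.

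**The concern.** The hypothesized spillover acts on children whose mothers were not counseled. The outcome that could show it averages those children with the ones whose mothers were counseled. If the primary hypothesis is true, the average moves in favor of the intervention even when nothing happens in the non-anemic children.

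A favorable prevalence difference could therefore be taken as support for the spillover pathway when it only repeats the primary result, diluted by the share of children who were not anemic at baseline. The protocol stresses how the intervention works, not only whether it works, and it looks ahead to scaling up. A mistaken inference about spread beyond counseled families would bear on both.

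**Working it through.** **Inputs (sample size section):** cure rate 30% control and 42% intervention; two-sided alpha 0.05; power 80%; ICC 0.05; 25 anemic children per village; 10% loss; 50% anemic at baseline. Thirty villages per arm.

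**1. The plan's own figures reproduce.**
- Per arm: [1.96 x sqrt(2 x 0.36 x 0.64) + 0.8416 x sqrt(0.30 x 0.70 + 0.42 x 0.58)]² / 0.12² = 250, so 500 in all.
- Design effect: 1 + 24 x 0.05 = 2.2; 500 x 2.2 = 1,100.
- Loss: 1,100 / 0.9 = 1,222, against 1,220 stated.
- Children of any baseline status: 610 / 0.5 = 1,220 per arm.

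**2. What the pooled outcome measures.** Let p be the share anemic at baseline, c the cure rate, and i the rate of new anemia among those not anemic at baseline. Six-month prevalence in an arm is p(1 − c) + (1 − p)i. The difference, control minus intervention, is

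D = p(c_int − c_con) + (1 − p)(i_con − i_int).

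The first term comes from the directly targeted children. Only the second comes from children who were not anemic at baseline.

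**3. No spillover (i equal in both arms).** The second term is zero.
- Persisting anemia, control: 0.50 x 0.70 = 35%.
- Persisting anemia, intervention: 0.50 x 0.58 = 29%.
- D = 0.50 x 0.12 = 6 points, whatever the common rate of new anemia.
- At an assumed baseline prevalence of 40% to 70%, D is 4.8 to 8.4 points.

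**4. Illustration.** The protocol gives no rate of new anemia; assume 20% in the control arm.

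| New anemia, control v intervention | Difference in non-anemic children | Pooled D |
|---|---|---|
| 20% v 10% | 10 points | 11 points |
| 20% v 15% | 5 points | 8.5 points |
| 20% v 20% | 0 | 6 points |
| 20% v 25% | −5 points | 3.5 points |

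In the last row the children not anemic at baseline do worse under the intervention, yet the pooled outcome still favors it.

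**The case against.** The best defense is that pooled prevalence is a proper target in its own right. In a village-randomized trial the overall effect on anemia among village children is standard and relevant to policy, and it contains the direct effect by definition. A reader might infer that outcome 5 is the designated test of spillover, but no section says so. The rationale says spillover would lower prevalence; it does not say that lower prevalence will be taken as proof of spillover. All of this stands, and it is a reason to keep the outcome. It does not remove the gap: outcome 5 is the only listed outcome that could reflect the stated spread, and it cannot separate that spread from the direct effect.

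A reader might also infer that leaving out severely anemic and non-enrolled children is why spillover cannot be shown. The documents do not support this. The group named in the mechanism, children without anemia, is enrolled and measured. The exclusion of severe anemia is the same in both arms; it limits generalization and calls for an accurate label, nothing more.

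Nor does it follow that the trial cannot answer the spillover question. Under Protocol of data collection, 6-month hemoglobin, dietary recall and adherence are obtained from all participants. A statistical analysis plan that is not shown may already define the comparison, so its absence from the article is not in itself the criticism.

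The misreading is also not certain to arise. If the ICC of 0.05 applies to prevalence and new anemia is 0 to 30% (both assumptions), power for a 6-point difference with 1,220 children per arm in 30 villages is about 41% to 45%; with an assumed ICC of 0.02 it is about 60% to 66%. A direct effect alone might miss significance. That lowers the chance of a misleading positive result, but the estimate would be no easier to interpret.

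Finally, a comparison in non-anemic children would not isolate mother-to-mother spread. The trained LHW also hands IFA to mothers of non-anemic children at the ADC, and a non-anemic child with an anemic sibling may have a counseled mother. This objection is right, and the fix allows for it.

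**Conclusion.** The point holds in limited form. As defined, outcome 5 is a total effect among enrolled children. Under the plan's own assumptions it differs by 6 points when spillover is zero, so a difference on it does not support the spillover hypothesis. This rests on the protocol's 50% baseline prevalence and 30% v 42% cure rates, and on equal new anemia in both arms as the meaning of no spillover. The size scales with baseline prevalence; the mixing of the two effects does not depend on it.

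The primary outcome is unaffected and the pooled outcome is not invalid. The change is a cheap improvement that should be made because it lets the trial address a hypothesis it states.

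**What to change.** - Add a secondary comparison between arms, among children not anemic at baseline, of 6-month anemia and 6-month hemoglobin. Use the planned GEE models with adjustment for the stratification factor.
- Where siblings can be identified, add a sensitivity analysis that leaves out children with an anemic enrolled sibling.
- State beforehand that the result is the indirect effect by any route, including contact with the trained LHW, and not mother-to-mother spread alone.
- Keep pooled prevalence as the total effect, and label it as prevalence among enrolled children without severe anemia at baseline.

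**Cost.** No new data, and one more secondary test. Precision is moderate. The plan implies 1,220 x 0.5 = 610 non-anemic children per arm, or 549 after 10% loss, which is 18.3 per village. If the ICC is 0.05 and control-arm new anemia is 20% (both assumptions), power is about 93% for 20% v 10% and about 36% for 20% v 15%. The estimate should be reported with its confidence interval, and a non-significant result should not be read as absence of spillover.

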### Protocol of recruitment

From the list of all children < 6 years registered in each village by the LHW in charge of the ADC, the research team will generate an eligible 12–59 month child list. Using this list, the LHW will mobilize participants and their mothers to the village ADC for study enrollment. Recruitment will occur at the village ADC and last for approximately 2 days. Additional house visits will be made on recruitment days to identify reasons for non-attendance of participants on the list (for example, those who are too sick, traveling, or migrating] and to help mobilize those who forgot to visit the ADC. Mothers/caregivers of all eligible children, who after being provided information about the trial indicate willingness to participate and an intention to live in the village for at least 6 months after enrollment, and those in the intervention arm indicating a willingness to receive LHW-led counseling will be enrolled after providing written informed consent (Fig. 1). Where recruitment is <80 % of the eligible list, an additional recruitment day will be allocated. Children who do not fulfill the inclusion criteria during recruitment sessions are not eligible for future recruitment.

### Protocol of data collection

At study entry, a baseline questionnaire will record participant information. An additional file shows this in more detail [see Additional file 1]. Participants will also have a baseline sample of anticoagulated venous blood obtained to detect anemia and measure serum ferritin. All recruited participants will have a hemoglobin value estimated using an automated cell counter (Sysmex 405, Transasia laboratory systems, Japan). Within a few days the research team will provide mothers/caregivers with results of the hemoglobin values and anthropometry, and cluster LHWs with a list of anemic and non-anemic children. The list will permit LHWs in each cluster to organize the delivery of dose appropriate IFA to anemic and non-anemic children and to identify mothers of anemic children for delivery of monthly education and counseling.

The date of delivery of the first month’s supply of IFA to the mothers of children in a cluster will herald the start of the intervention in that cluster. LHWs will deliver IFA to mothers of non-anemic children at the ADC during routine monthly visits. LHWs will typically deliver IFA together with education and counseling to mothers of anemic children at their homes. From the second visit onward, adherence data will be collected by the LHW, and the remaining IFA pills/empty strip will be obtained from the mother. In the control arm, LHWs will deliver IFA as usual in the setting of the ADC and will not deliver education and counseling to mothers of anemic children or collect monthly IFA adherence data. Approximately 6 months from the day of delivery of the first IFA supplement, the research team will perform a follow-up visit to collect 24-hour dietary recall data, anthropometry, and information on adherence to IFA in the previous month from all enrolled participants. During this time, a repeat phlebotomy to estimate hemoglobin is performed for all participants in the cluster, and the trial is completed.

Questionnaires prior to and after the intervention from mothers of anemic children provide information about the impact of LHW-delivered education and counseling on the mother’s knowledge regarding anemia and its effects on the child. The mother’s knowledge and practice questionnaire was explored by pilot testing it in the field for ease of administration and understanding. Assessment of 24-hour dietary iron intake at baseline and at the end of the intervention will provide information to estimate the effect of this intervention on promoting dietary diversification and improving dietary iron content. Finally, assessments of ferritin, a serum marker of iron stores, will provide information on whether actual improvements have been made in the total body iron stores of anemic children.

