#### Lay health worker training

LHWs in the intervention villages [*n* = 30] will receive training under four separate hands-on workshops over a period of 6 months. Training will occur with the use of role play, facilitation, and flip charts to help develop counseling and education skills of the LHWs. Training will take place at a location different from the LHWs’ habitual training/supervision sites, to minimize the risk of contamination. LHWs will be trained to deliver five monthly education and counseling sessions to mothers/caregivers of anemic children. Specifically, these sessions will aim to improve mothers’ knowledge regarding anemia and its consequences, the treatment of iron deficiency anemia with IFA, the importance of adherence to IFA treatments, sources of iron-rich food, diet modification behaviors, and hygiene. The possibility of contamination during LHW-supervisor monthly meetings, due to interaction between control group and intervention group LHWs, is minimal. LHWs in the control group neither receive training nor have access to training and intervention materials and will therefore be unable to replicate the intervention in their villages.

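### The dietary iron outcome is said to show dietary diversification, which an iron quantity does not measure, and its contrast and population are worded differently across sections

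*Protocol article*

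**What the plan says.** In the Protocol article, Protocol of data collection begins the relevant sentence with "Assessment of 24-hour dietary iron intake at baseline and at the end of the intervention will provide information to estimate the effect", and the sentence goes on so that, in full, this assessment will "provide information to estimate the effect of this intervention on promoting dietary diversification and improving dietary iron content". For month 6 the same section says that "the research team will perform a follow-up visit to collect 24-hour dietary recall data", and it includes every enrolled child.

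The Outcomes section defines the second secondary outcome as "differences in the estimated 24-hour dietary iron intake among anemic participants exposed and not exposed to the intervention". It does not mention baseline. Three of the other four secondary outcomes are worded as change: knowledge is a "difference in changes of knowledge and practice of mothers of anemic children from baseline to follow-up", hemoglobin is a "difference in net improvements in individual hemoglobin values between baseline and 6 month follow-up", and ferritin is given as net improvement. No food-group, food-source or other diversity measure is listed.

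The Abstract (Methods and design) lists dietary iron intake among secondary outcomes compared in all participants of both arms. Outcomes limits it to anemic children.

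The counseling covers, among other things, "sources of iron-rich food, diet modification behaviors, and hygiene" (Lay health worker training). Under Components of the Intervention, only mothers or caregivers of anemic children in the intervention arm receive the five monthly sessions. The protocol gives no SD, target difference or power for dietary intake.

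**The concern.** There are three linked issues.

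- **Measure and claim do not match.** The claim covers both diversification and iron content, but the measure is an iron quantity. The Background itself treats low iron content of food and too little animal protein as separate dietary problems.
- **The comparison is not the same in each place.** One section implies a difference between arms, another uses both time points, and the Abstract names a different population. These are different analyses of the same recall data.
- **The reporters differ by arm.** The children are 12–59 months old, so the respondent is in practice the mother or caregiver. In the children being compared, those caregivers have been taught which foods are desirable in one arm only.

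At stake is how a dietary result would be read. Both arms receive IFA and the intervention also works on adherence, so cure rate cannot separate diet from tablets. Dietary intake is the listed outcome closest to the diet step of the causal pathway.

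**Working it through.** **1. The protocol's own figures (Statistical power and sample size calculation).** Inputs are cure rates of 30% and 42%, two-sided alpha 0.05 and 80% power. With a pooled proportion of 0.36, n per arm = [1.960·√(2·0.36·0.64) + 0.842·√(0.30·0.70 + 0.42·0.58)]² / 0.12² = 250, or 500 in all, as stated. The design effect is 1 + (25 − 1)·0.05 = 2.2, which gives 1,100, as stated. Allowing for 10% loss, 1,100/0.9 = 1,222, against 1,220 stated. These figures reproduce and do not depend on the dietary outcome.

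**2. Iron against diversity.** Write iron intake as I = Σ aᵢcᵢ (amount eaten times iron content, summed over foods) and diversity as D = the number of food groups with aᵢ > 0.
- Multiply every amount by k > 1: I rises by the factor k and D is unchanged.
- Replace part of one food by a food from a new group carrying the same iron: I is unchanged and D rises by one.

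So I does not determine D in either direction. The recall forms may well hold what is needed to compute D, but the outcome as defined does not use it.

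**3. The sections side by side.**
- Time points: Outcomes names none for diet; Protocol of data collection names baseline and end.
- Population: Outcomes says anemic children; the Abstract says all participants. The recall is collected from all enrolled children, so either is feasible and the text has to choose.

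**4. What baseline adjustment buys.** The protocol gives no correlation r between baseline and month-6 intake, so r is assumed. I also assume 1,100/2 = 550 children per arm, the design effect of 2.2 carried over from the primary outcome, and the same instrument at both visits.
- Effective n per arm = 550/2.2 = 250. In SD units, SE = √(2/250) = 0.0894. The detectable difference at 80% power is 0.0894·(1.960 + 0.842) = 0.25 SD for month 6 alone.
- With baseline as covariate, the variance is multiplied by 1 − r². At r = 0.3 this removes 9% (detectable difference 0.239 SD); at r = 0.5 it removes 25% (0.217 SD).
- With a change score, the variance is multiplied by 2(1 − r). At r = 0.3 the factor is 1.4 (0.296 SD); at r = 0.5 it is 1.0 (0.251 SD). A change score is therefore less precise than month 6 alone when r < 0.5.

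**5. What differential reporting could do.** Suppose there is no true effect and counseled caregivers over-report by b SD (assumed). The false-positive rate is 1 − Φ(1.96 − b/SE) + Φ(−1.96 − b/SE). With SE = 0.0894:
- b = 0.05: about 9%
- b = 0.10: about 20%
- b = 0.20: about 61%

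Counseling takes place after baseline, so the shift stays in a baseline-adjusted estimate. With r = 0.5, SE = 0.0894·√0.75 = 0.0775; for b = 0.10, b/SE = 1.29 and the rate is about 25%. Adjustment narrows the interval around the same biased value.

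**The case against.** The best defense is that the article condenses a fuller protocol. Diversification appears in one descriptive sentence and is not an endpoint, food-group coding of the recall may be specified elsewhere, and how baseline enters a secondary analysis is ordinarily left to an analysis plan. The follow-up recall is taken by the research team, not by the counseling health worker, and ferritin is already planned as an objective marker. Much of this stands. The absence of an adjustment method is not a finding. What remains is that the article's own sections disagree on contrast and population, and that one sentence assigns the iron measure a task it cannot do. An independent interviewer helps, but does not undo what the respondent has been taught.

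Several stronger readings are tempting and are not supported.
- **That the baseline recall is ignored.** The data-collection sentence expressly includes baseline; only Outcomes is silent.
- **That a positive result would be reporting alone, or that over-reporting has a known direction and size.** The protocol gives no such figure. The shifts above are assumptions.
- **That the Discussion's causal-chain and diet-focused statements rest on this outcome.** They refer to the pathway and the intervention as a whole. The knowledge outcome also covers practice, which may include diet; its items are not shown.
- **That ferritin should decide whether a dietary effect is real.** Adherence counseling and monthly pill counts take place only in the intervention arm, so ferritin could rise through better tablet-taking with no change in diet.

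**Conclusion.** The point holds in a limited form. Dietary iron intake can address iron content but not diversification, and no diversity measure is listed. The sections do not agree on whether the comparison uses baseline or on which children it covers. Differential reporting is a plausible risk of unknown size that baseline adjustment cannot remove.

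The numbers are illustrative. The variance gain of 9–25% depends on r = 0.3–0.5. The false-positive rates of about 9%, 20% and 61% depend on assumed shifts of 0.05, 0.10 and 0.20 SD, 550 children per arm and a design effect borrowed from the primary outcome. The primary outcome and the sample size are not touched. This is a low-severity clarification that makes a secondary claim safer.

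**What to change.** - In Outcomes, define the second secondary outcome as month-6 24-hour iron intake compared between randomized arms in children anemic at baseline, with baseline intake as a covariate in the clustered linear model. Align the Abstract and Protocol of data collection with it. Naming the randomized arms also avoids any as-treated reading of the exposure wording.
- From the same recall data, prespecify a food-group count and any animal-source food (yes/no) as the diversification measure. Otherwise delete diversification from the data-collection sentence.
- Report the result as caregiver-reported intake. Interpret it alongside ferritin and the month-6 IFA adherence assessment, which is made in both arms. Do not make ferritin a condition for a dietary conclusion.

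The cost is wording and some extra coding of recall forms, with no new visits or measurements. The downside is a more cautious dietary claim.
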